### Enrollment procedures

Participants will be enrolled in batches of approximately 20–30 to facilitate scheduling and to maintain balanced allocation across study arms via stratified block randomization. During the 3 weeks prior to randomization, baseline assessments will be completed for each batch to confirm eligibility.

Before any study-specific procedures, the Principal Investigator (PI) or a designated study coordinator will obtain written informed consent after explaining the trial's objectives, procedures, and potential risks and benefits. Eligibility screening, based on predefined inclusion and exclusion criteria, will be conducted by trained personnel. To minimize attrition and support adherence, participants will receive advance scheduling information, regular reminders, and logistical support as needed.

### Randomization

After written informed consent and baseline assessments, participants will be randomized by an off-site research assistant using a computer-generated sequence in SPSS (fixed permuted blocks of 8) in a 1:1:1:1 ratio to 2 Hz TENS, 100 Hz TENS, placebo TENS, or a no-TENS usual-care control. Allocation concealment will be ensured with sequentially numbered, opaque, sealed envelopes prepared by personnel independent of enrollment and assessment. Stratified block randomization will be used by Brunnstrom stage (III/IV/V), sex (male/female), stroke type (ischemic/hemorrhagic), and lesion side (left/right). Outcome assessors will remain blinded to group assignment.

To support participant blinding between active and sham arms, the placebo TENS device will be identical in appearance and procedures, will deliver a brief ramp-up to a just-perceptible tingling (~20–30 s), and will then fade to an imperceptible output while maintaining visual cues. Participants in the no-TENS control arm will not be blinded; TENS operators cannot be blinded due to device setup and will not perform outcome assessments. Electrode placement will follow a predefined protocol by Brunnstrom stage (e.g., wrist extensors in stage III; finger extensors/supinators in stage IV; intrinsic hand muscles in stage V). All operators will receive standardized training to ensure consistent application.

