### Study sample

Based on a preliminary RCT (23) investigating TENS for post-stroke upper-limb motor rehabilitation, the sample size was derived using a moderate standardized effect size (*d* = 0.5) on the primary endpoint (FMA-UE), two-sided α = 0.05, and power (1–β) = 0.80. The required sample is 128 participants (32 per group). Allowing for ~20% attrition, the target enrollment is 156 (39 per group).

A total of 156 participants will be recruited from the Rehabilitation Department of Shenzhen Bao'an District Fuyong People's Hospital. Inclusion criteria are: (1) age 40–80 years; (2) clinically confirmed ischemic or hemorrhagic stroke 10 days to 2 months prior to enrollment; (3) Brunnstrom stage III–V for upper-limb motor recovery (mild to moderate impairment); (4) baseline FMA-UE 15–55; (5) able to perform ≥ Grade 2 voluntary movement (gravity-eliminated) in the paretic upper limb on MMT.

Exclusion criteria include: (1) any uncontrolled or unstable medical, cardiovascular, neurological, or orthopedic condition that could interfere with rehabilitation or study participation; (2) contraindications to TENS (e.g., implanted pacemaker, metal near the stimulation site, active skin lesions, known electrode allergy); (3) severe receptive aphasia, MoCA < 20 indicating moderate–severe cognitive impairment, or any psychiatric illness that could interfere with understanding instructions or providing informed consent; (4) clinically significant peripheral neuropathy of the paretic upper limb, diagnosed clinically or via electrophysiology; (5) concurrent participation in another interventional clinical trial or use of investigational drugs; (6) severe contractures/deformities or fixed joint limitations of the shoulder, elbow, wrist, or fingers that preclude voluntary movement or electrode placement; (7) Brunnstrom stage I–II of the upper limb.

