A key strength of this study lies in its individualized stimulation strategy guided by the Brunnstrom stages of motor recovery. Electrode placement will be tailored to target muscle groups that are most functionally relevant at each stage—for example, stimulating wrist extensors in stage III to disrupt flexor synergy, finger extensors and supinators in stage IV to promote distal coordination, and intrinsic hand muscles in stage V to enhance fine motor control. This stage-specific approach reflects the neurorehabilitation principle that task-relevant, peripheral sensory input can facilitate use-dependent plasticity and promote reorganization of motor pathways. By aligning stimulation targets with the evolving motor status of the patient, the protocol aims to optimize the neuromodulatory effects of TENS in a phase-specific and personalized manner.

The inclusion of both a placebo group and a no-TENS usual-care control group strengthens the internal validity of this trial by enabling a clearer distinction between true neuromodulatory effects and nonspecific influences such as attention, expectation, or spontaneous recovery. Moreover, stratified randomization based on Brunnstrom stage, sex, stroke type, and lesion side was employed to ensure balanced baseline characteristics across groups, further reducing the risk of allocation bias and enhancing the reliability of outcome comparisons.

Despite its methodological strengths, this study has several limitations. First, as a single-center trial, the generalizability of the findings may be limited due to potential center-specific clinical practices or population characteristics. Second, neurophysiological measures such as transcranial magnetic stimulation (TMS), or functional magnetic resonance imaging (fMRI) were not included, restricting our ability to explore the underlying cortical mechanisms of TENS-induced motor recovery. Third, although the follow-up period extends to 3 months post-intervention, this duration may be insufficient to evaluate long-term outcomes or the sustainability of treatment effects. Lastly, while the sample size is adequately powered for primary comparisons, it may be insufficient for detecting significant differences in subgroup analyses, particularly those stratified by Brunnstrom stage.

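### Twenty-four strata with fixed blocks of 8 are too many for 156 participants: the scheme reduces imbalance but does not ensure it, and arm sizes drift from 39

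*Protocol article*

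**What the plan says.** The Randomization section fixes every element of the scheme. The sequence is computer-generated with "fixed permuted blocks of 8", "in a 1:1:1:1 ratio to 2 Hz TENS, 100 Hz TENS, placebo TENS, or a no-TENS usual-care control". The strata are defined in the same paragraph: "Stratified block randomization will be used by Brunnstrom stage (III/IV/V), sex (male/female), stroke type (ischemic/hemorrhagic), and lesion side (left/right". Allocation is by an off-site research assistant, with concealment by numbered sealed envelopes.

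The Study sample section gives the number to be allocated: "the target enrollment is 156 (39 per group".

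Two statements describe what the scheme is meant to achieve. Enrollment procedures says that participants enter in batches of about 20–30, among other reasons "to maintain balanced allocation across study arms via stratified block randomization". The Discussion says that the stratification "was employed to ensure balanced baseline characteristics across groups".

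The article does not mention sparse strata, smaller or varying blocks, or a limit on arm-size differences.

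**The concern.** Stratified blocks force balance only where blocks are completed. In a stratum that ends part-way through a block, the last few allocations are whatever came first in a random permutation. With many strata and long blocks, these leftovers add up across strata, so both arm sizes and the factor margins drift.

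Three things are at stake: the accuracy of the two balance statements, how close the arms come to their target size, and balance on Brunnstrom stage. Stage deserves attention because it determines electrode site (Intervention details) and defines the prespecified subgroups (Analysis). It is also the one stratification factor missing from the covariates listed under Statistical analysis; sex, stroke type and side are there.

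**Working it through.** **Inputs from the document.** N = 156; four arms, 1:1:1:1; block size 8 (two per arm); factors with 3, 2, 2 and 2 levels.

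**The plan's own figure.** 32 per group × 1.2 = 38.4, rounded up to 39; 39 × 4 = 156. This reproduces the target enrolment.

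**Arithmetic that needs no assumption.**
- Strata: 3 × 2 × 2 × 2 = 24.
- Mean per stratum: 156 / 24 = 6.5, below one block of 8.
- Blocks available: 156 / 8 = 19.5, so at most 19 of the 24 strata can complete a block, even under the most favourable split.

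**Results that need an assumed factor mix.** The document gives no prevalences, so several mixes were tried. They run from an even mix to a strong skew (stage 50/30/20%, 70% male, 85% ischemic).
- Strata with fewer than 8 participants: the expected number is the sum over strata of P(X ≤ 7), with X binomial (n = 156). It is 16.2 of 24 for the even mix and 15.6–16.3 for the skewed mixes.
- Participants in incomplete blocks: about 93 of 156 (60%) for the even mix, 78 (50%) for an intermediate mix, and 65 (42%) for the strong skew.

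**Simulation of the stated scheme** (4,000 trials per mix; key results confirmed in a separate run):
- Arm size: SD 2.5–2.7, 95% range 34–44 around 39.
- Largest minus smallest arm: mean about 6, 95th percentile 10–11.
- Some arm at 35 or fewer: about one trial in three.
- Stage III counts in the 2 Hz and 100 Hz arms differing by 4 or more: about 13–18% of trials.

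**Comparison of schemes.** The factor gap is the mean absolute difference in prevalence between the 2 Hz and 100 Hz arms, in percentage points.

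| Scheme | Mean arm gap | Factor gaps |
|---|---|---|
| Simple randomisation | about 13 | about 7–9 on all factors |
| Stated: 24 strata, blocks of 8 | about 6 | about 4–5 on all factors |
| 24 strata, blocks of 4 | about 4.6 | about 3–4 on all factors |
| Stage only, blocks of 8 | about 2 | about 1.5 on stage; 6.4–9.0 on sex, stroke type and side |
| Minimisation with a random element, four factors | about 1 | about 2 on all factors |

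The minimisation row assumes that the arm giving the smallest total marginal range is taken with probability 0.8, and that otherwise an arm is drawn at random from all four.

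**Power cost.** At d = 0.5, two-sided 0.05, before attrition, 39 vs 39 gives 58.7% power for 100 Hz vs 2 Hz. Averaged over the arm sizes that the stated scheme produces, power is 58.5–58.6%; at the 5th percentile it is about 55.8%. The mean loss is therefore 58.7 − 58.6 = 0.1 to 58.7 − 58.5 = 0.2 points.

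**The case against.** The strongest reply is that little harm follows. The scheme is a valid randomisation, it beats simple randomisation on arm size and on all or nearly all factors, the mixed model does not need equal arms, and three of the four factors are adjusted for anyway. All of that stands, and it rules out several stronger readings.

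- A reader might infer that uneven arms materially weaken the primary comparison. They do not: the average loss is 0.1–0.2 points. That power is only 58.7% even with equal arms comes from the sample size, which is a separate matter.
- A reader might infer bias. Nothing in the scheme favours one arm.
- A reader might take 39 per group as a requirement. The article presents it as a target with an attrition allowance, so drift away from it breaks no rule.
- A reader might say that at least half of the participants are always in incomplete blocks. Under the strong skew the figure is 42%.
- A reader might argue from batches of 20–30 spread over 24 strata, about one person each. Nothing says that the lists restart with each batch, so this bears only on balance within a batch.
- A reader might conclude that stratifying on stage alone is the obvious cure. It improves stage and arm size, but it leaves sex, stroke type and side at about the imbalance of no stratification.

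The stage subgroups are also declared exploratory, so a stage III difference of 4 or more does not undermine a confirmatory result. What the reply does not rescue is the wording of the balance statements, or the choice of a scheme that a simple alternative improves on for arm size and every factor.

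**Conclusion.** The concern holds as a design inefficiency and an overstated claim, not as a threat to validity. The number of strata, the block size and N are all fixed in the article and do not fit together: 6.5 participants per stratum against a block of 8. That most strata fall short was near-certain under every mix tried (more than half did so in over 99% of simulated trials), but the exact percentages depend on assumed prevalences. Balance is improved, not ensured, and arm sizes are held only loosely near 39.

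**What to change.** Have the off-site research assistant allocate each participant by minimisation with a random element over the same four factors: Brunnstrom stage, sex, stroke type and lesion side. State the probability of following the minimising arm, and keep the sequence and algorithm inaccessible to those who enrol and assess. Because stage would then be an allocation factor, add it to the covariates of the primary model; the other three are already listed.

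The cost is operational. Pre-filled envelopes no longer work, so the assistant must be reachable and must release each assignment in sequence after baseline assessment.

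If envelopes must stay, blocks of 4 within the same strata are a partial repair: the mean arm gap falls from about 6 to about 4.6, and the chance of an arm at 35 or fewer falls to 12–15%.

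If the stated stratified-block scheme stays in any form, the statements in Enrollment procedures and the Discussion should say that stratification is intended to reduce imbalance, not that it ensures balance. That costs only an edit.

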### Statistical analysis

All analyses will be performed in SPSS 27.0 on the intention-to-treat set. Baseline characteristics will be compared with one-way ANOVA or Kruskal–Wallis tests (continuous) and chi-square or Fisher's exact tests (categorical). The primary endpoint is FMA-UE; the primary comparison is 100 Hz vs. 2 Hz at week 8. Longitudinal changes will be analyzed using a linear mixed-effects model with random intercepts (participants), fixed factors group (2 Hz, 100 Hz, placebo, control) and time (baseline, week 4, week 8, 1 month post-discharge, 3 months post-discharge), and the group × time interaction; prespecified covariates (age, sex, time since stroke, stroke type, side of hemiplegia) will be included. Other pairwise contrasts will be adjusted using the Holm method; Brunnstrom-stage subgroup analyses will be exploratory via interaction terms. Secondary continuous outcomes will use the same LMM; ordinal outcomes (MMT, MAS, Lindmark) will use proportional-odds mixed models. Missing data will not use LOCF; inference will rely on the LMM under MAR with multiple-imputation sensitivity.

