### Follow-up timepoints and assessment procedures

Follow-up assessments are scheduled at 1 month and 3 months after completion of the 8-week intervention. The selection of these timepoints was based on both clinical and neurophysiological considerations (35). The 1-month follow-up corresponds to the early consolidation phase of motor recovery, during which short-term neuroplastic changes may stabilize or continue to evolve. The 3-month timepoint is commonly used in stroke rehabilitation research to evaluate the sustainability of treatment effects, as it reflects a period when spontaneous recovery tends to plateau and long-term functional gains—if present—can be more clearly attributed to the intervention. These intervals are supported by previous randomized controlled trials examining post-stroke motor rehabilitation outcomes.

All follow-up evaluations will be conducted in person at the Rehabilitation Department of Shenzhen Bao'an District Fuyong People's Hospital. Assessments will be performed by certified physical and occupational therapists with at least 3 years of clinical experience in stroke rehabilitation. To ensure consistency and reliability across timepoints, all assessors will undergo structured training in the administration and scoring of each outcome measure prior to participant enrollment. Inter-rater reliability will be reinforced through pilot calibration sessions and ongoing periodic reviews. The same assessor will be assigned to each participant across baseline and follow-up assessments whenever feasible, to minimize inter-observer variability. All assessment procedures will follow a standardized operating protocol and will be documented using unified case report forms.

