### Analysis

The primary outcome will be the change in FMA–UE from baseline to week 4, week 8, 1 month post-discharge, and 3 months post-discharge. The primary contrast will be 100 Hz vs. 2 Hz at week 8; other time-point contrasts will be supportive/exploratory.

A prespecified subgroup analysis by Brunnstrom stage (III/IV/V) will examine whether frequency effects differ by motor-recovery stage (exploratory interpretation). Within the FMA–UE, we will also explore segment/domain effects (proximal vs, distal components and the coordination/speed subscale).

Secondary outcomes will include MMT (wrist flexor/extensor strength), MAS (wrist-flexor spasticity), Lindmark Motor Score—hand subscale (grasp), and the Barthel Index (ADLs). These measures complement the FMA–UE by capturing muscle strength, spasticity, hand function, and functional independence.

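### The random-intercept-only primary model forces one variance and one correlation on all five visits, so the standard error of the week-8 change contrast may be wrong in either direction

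*Protocol article*

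**What the plan says.** In the protocol article, the Statistical analysis section specifies a "linear mixed-effects model with random intercepts (participants), fixed factors group (2 Hz, 100 Hz, placebo, control) and time". Time has five levels, from baseline to the second follow-up, and a group-by-time interaction is included. No random slope, residual covariance structure or robust standard error is named. The primary comparison is 100 Hz against 2 Hz at week 8.

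The Analysis section puts the outcome on the change scale: "The primary outcome will be the change in FMA–UE from baseline to week 4, week 8, 1 month post-discharge, and 3 months post-discharge". It repeats that the primary contrast is at week 8.

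Three other places bear on the covariance:

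- **Study sample:** stroke occurred between 10 days and 2 months before enrolment.
- **Table 1:** the visits fall at months 0, 1, 2, 3 and 5.
- **Follow-up timepoints and assessment procedures:** the 3-month follow-up, which is month 5, was chosen because "it reflects a period when spontaneous recovery tends to plateau". For the 1-month follow-up, month 3, the same section allows that changes could either settle or carry on.

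**The concern.** A participant random intercept with independent residuals is compound symmetry. Every visit has the same variance, and any two visits have the same correlation however far apart they are. In early stroke recovery, people improve by different amounts while recovery is under way and later level off. Correlations between baseline and later visits can then differ from correlations among the later visits, and variances can change over time.

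The model averages over all of this. With baseline as a time level and change as the outcome, the week-8 test is a group-by-time contrast. Its standard error comes entirely from the pooled residual variance, not from the variability of the baseline-to-week-8 change itself. If the two differ, the p-value and confidence interval of the primary contrast are wrong. Too small a standard error raises the false-positive rate, and too large a one loses power.

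**Working it through.** **Inputs from the documents.** Four equal arms; visits at months 0, 1, 2, 3 and 5; random intercepts only; change from baseline to week 8; two-sided 5% level. The documents give no SD or between-visit correlation, and the sample-size paragraph states only a standardized effect. There is thus no figure of the plan's own to reproduce here, and every SD and correlation below is an assumption.

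**Formulas (balanced data).**

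- Change variance under the fitted model: 2 × (mean variance − mean covariance over the five visits).
- True change variance: v(baseline) + v(week 8) − 2 × cov(baseline, week 8).
- SE ratio = √(modelled ÷ true). The sample size cancels.
- Type I error = 2 × [1 − Φ(1.96 × SE ratio)].

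**Worked example.** SD 12 at baseline and 14 afterwards; correlation 0.7 between baseline and later visits, 0.9 among later visits.

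- Mean variance: (144 + 4 × 196)/5 = 185.6.
- Covariances: 0.7 × 12 × 14 = 117.6 (4 pairs) and 0.9 × 196 = 176.4 (6 pairs). Mean: (470.4 + 1058.4)/10 = 152.88.
- Modelled change variance: 2 × (185.6 − 152.88) = 65.44.
- True change variance: 144 + 196 − 2 × 117.6 = 104.8.
- SE ratio: √(65.44/104.8) = 0.79. Type I error: 12.1%.

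**Range of patterns.** The plateau rows assume score = personal intercept (SD 11) + personal recovery (SD 8) × (1 − e^(−t/τ)) + error, with t and τ in months.

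| Assumed truth | SE ratio | Type I error |
|---|---|---|
| Compound symmetry | 1.00 | 5% |
| Baseline–later 0.8, later–later 0.85 (SD 12/14) | 0.95 | 6.4% |
| 0.8 / 0.9 (SD 12/14) | 0.85 | 9.4% |
| 0.7 / 0.9 (SD 12/14) | 0.79 | 12.1% |
| 0.7 / 0.95 (SD 12/14) | 0.72 | 16.1% |
| Plateau, τ = 0.5, error SD 2 | 0.68 | 18.4% |
| Plateau, τ = 1, error SD 2 | 0.73 | 15.5% |
| Plateau, τ = 1.7, error SD 2 | 0.82 | 10.8% |
| Plateau, τ = 2, error SD 2 | 0.86 | 9.3% |
| Plateau, τ = 3, error SD 2 | 0.94 | 6.4% |
| Plateau, τ = 1.7 to 3, error SD 4 | 0.89–0.97 | 8.0% down to 5.7% |
| Correlation decaying by 0.7–0.95 per month | 1.02–1.08 | 4.5% down to 3.4% |
| Linear personal slopes, SD 1–2 per month, error SD 2 | 1.13–1.25 | 2.6% down to 1.4% |

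**Matching the plateau rows to the article's timeline.** The share of recovery completed by time t is 1 − e^(−t/τ). With τ = 1, 95% is complete by month 3, and with τ = 0.5 nearly all of it. With τ = 1.7, 83% is complete at month 3 and 95% at month 5; with τ = 3, 63% and 81%. Flattening around month 5, where the article places it, therefore corresponds to τ of about 1.7 to 3 and an error rate of about 6–11%.

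**Raw week-8 difference.** The model then uses the mean variance in place of the week-8 variance. For SD 12/14 the SE ratio is √(185.6/196) = 0.97, giving 5.6%. Across the patterns examined, the formula gives 3.9–6.1%.

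**Simulation.** Four arms of 39, REML fit of the planned model, 1,500 runs per scenario, with no dropout and with 20% monotone dropout. These runs used equal SDs unless stated.

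- 0.8/0.9: 9.1–10.3%. 0.7/0.9: 11.6–13.0%. 0.7/0.95: 16.6–17.1%.
- Plateau, τ of 0.5 to 1: 15.5–18.1%.
- Monthly decay of 0.9: 3.3–4.0%. Linear slopes with SD 2: 1.4–1.9%.
- Raw week-8 difference: up to 7.1%, with SDs rising over time.
- Week-8 change tested on its own variance, as an unstructured covariance would do: 3.9–5.9% throughout. Simulation error at 5% is 1.96 × √(0.05 × 0.95/1500) = 1.1 points, so this is nominal.

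**The case against.** Four points can fairly be made for the plan.

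1. **The residual structure is not stated.** SPSS MIXED allows a random intercept together with a structured residual, and an unseen SAP may add one. This possibility is real. But the article names random intercepts as the only within-participant structure, and the plain reading of that is compound symmetry. The point concerns the model as stated.

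2. **The direction is not established.** This stands. A reader might infer that the interval is most likely too narrow. The documents give no variances or correlations, and smooth decay or steadily diverging slopes would make the test conservative.

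3. **The size is easily overstated.** This also stands. A reader might infer that the false-positive rate is two or three times 5%. That needs individual recovery to have largely flattened by weeks 4–8. The article ties the plateau only to the 3-month follow-up and leaves open continued change at the 1-month follow-up. Milder correlation gaps, such as 0.8 against 0.85, give only 6–7%.

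4. **The contrast is not pinned to a model coefficient.** Both analysis sections say 100 Hz against 2 Hz at week 8. Tested as a plain group difference at that visit, the error rate stays close to nominal. The change reading is still reasonable, because the Analysis section defines the outcome as change.

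A reader might also extend the concern to the Barthel Index and EEG measures, since secondary continuous outcomes use the same model. The recovery argument and the calculations concern FMA-UE only, so no size can be claimed for those outcomes.

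**Conclusion.** The concern holds as a risk of uncertain direction. The stated model puts compound symmetry on a primary change contrast measured across early stroke recovery, where that structure is unlikely to hold.

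On assumed SDs and correlations, type I error for the week-8 change contrast is:

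- about 6–11% if individual recovery flattens around month 5, the reading closest to the article's own account;
- up to 12–18% if recovery has largely flattened by weeks 4–8;
- about 1–4% under smooth correlation decay or linear divergence, which means lost power;
- 5% if compound symmetry is true.

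If the contrast is a raw week-8 difference, the error rate is near 5%, and up to about 7% in simulation. The documents do not support a claim of certain inflation or of a doubled or tripled error rate. Because an available alternative protects against error in both directions, the change is worth making before unblinding.

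**What to change.** Replace the random intercept with an unstructured 5×5 within-participant covariance (SPSS MIXED, REPEATED visit, covtype UN), with Satterthwaite or similar small-sample degrees of freedom. Prespecify the fallback order if the model does not converge, for example heterogeneous Toeplitz and then heterogeneous AR(1). In the same sentence, state whether the primary contrast is the difference in change from baseline or the group difference at week 8. Settle this before unblinding, so that the covariance is not chosen with the results in view.

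The cost is SAP wording. The structure has 5 × 6/2 = 15 covariance parameters, which 156 planned participants can support. Precision falls slightly only if compound symmetry is in fact true.

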**Figure 1 F1:**
[figure not shown]
Anticipated CONSORT flow diagram for participant recruitment and allocation.

The primary outcome is the FMA-UE, which evaluates motor control from proximal to distal segments and the transition from synergistic to isolated movements in stroke survivors (15). The FMA-UE has demonstrated excellent inter-rater (ICC = 0.997) and intra-rater reliability (ICC = 0.993) (16).

Secondary outcomes include:

Muscle strength of wrist flexion and extension, assessed by MMT, rated on a scale from 0 (no contraction) to 5 (normal strength). MMT has shown strong inter-rater reliability when performed by trained evaluators across various conditions (17).Spasticity of the wrist flexors, measured using the Modified Ashworth Scale, which exhibits good intra-rater reliability in patients with upper limb hemiparesis (18).Hand grasp function, evaluated using a subscale of the Lindmark Motor Score, a valid and reliable measure of hand motor function (19).Functional independence, assessed by the Barthel Index, which evaluates performance in basic activities of daily living and is widely used in stroke research and clinical practice (20).Cortical excitability and interhemispheric balance, measured using resting-state EEG. EEG signals will be recorded with standard 10–20 electrode placement, focusing on α (8–13 Hz) and β (13–30 Hz) band power at C3 and C4 electrodes. The α/β power ratio between C3 and C4 will be computed to assess hemispheric balance. These EEG markers have been widely used to reflect motor cortex activation and neuroplasticity changes following neuromodulatory interventions in stroke patients (21, 22).

Covariates include age, sex, body mass index (BMI), time since stroke onset, type of stroke (ischemic or hemorrhagic), and side of hemiplegia (left or right). Outcome assessors and the statistician will be blinded to group allocation. A detailed timeline and classification of outcome measures are provided in Table 1.

**Table 1 T1:** Schedule of assessments and outcome measures across study timepoints.

	**Before-intervention**	**Mid-intervention**	**Post-intervention**	**1-mo follow-up**	**3-mo follow-up**
**Time (Months)**	**0**	**1**	**2**	**3**	**5**

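### The week-8 primary contrast is not tied to one model term, and neither candidate term uses baseline FMA-UE efficiently

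*Protocol article*

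**What the plan says.** The Statistical analysis section names endpoint and comparison together: "The primary endpoint is FMA-UE; the primary comparison is 100 Hz vs. 2 Hz at week 8". The model is a "linear mixed-effects model with random intercepts (participants"), with fixed effects for group, for "time (baseline, week 4, week 8, 1 month post-discharge, 3 months post-discharge), and the group × time interaction". On covariates it states that "prespecified covariates (age, sex, time since stroke, stroke type, side of hemiplegia) will be included". Baseline FMA-UE is not among them. The covariate list in the design overview, below Figure 1, adds BMI but not baseline FMA-UE: "Covariates include age, sex, body mass index (BMI), time since stroke onset, type of stroke (ischemic or hemorrhagic), and side of hemiplegia (left or right"). Neither place says that the arms share a common baseline mean.

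The separate Analysis section, after Data and safety monitoring, describes the outcome as a change: "The primary outcome will be the change in FMA–UE from baseline to week 4, week 8" and the two follow-up visits. It repeats that the primary contrast is 100 Hz against 2 Hz at week 8.

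Table 1 schedules FMA-UE at baseline for every participant, and eligibility allows baseline scores from 15 to 55 on the 66-point scale.

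**The concern.** In a model with baseline as a time level and a free group-by-time interaction, two different quantities can be called the week-8 comparison. One is the difference between arms in mean score at week 8. The other is that difference minus the difference at baseline. The two estimates differ by exactly the observed baseline difference between the 100 Hz and 2 Hz arms, so the same data can give two primary estimates and two p-values. A primary test should not leave that choice open.

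The second issue is efficiency. Baseline FMA-UE is measured on everyone and eligibility permits a wide spread. Yet the model neither conditions on it nor uses the fact that randomized arms have the same expected baseline. The raw contrast ignores baseline. The change contrast subtracts it in full, which is more than the optimal amount whenever the correlation is below 1.

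**Working it through.** **Inputs.** Two of four equally allocated arms are compared, with n = 32 per arm after attrition (Study sample). A random intercept implies equal variance σ² at each visit and one common correlation ρ between visits. The documents do not give ρ, so it is assumed over 0.3 to 0.9. Complete data are assumed, with no credit for the listed covariates.

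**The plan's own figure.** The Study sample section assumes a "moderate standardized effect size (*d* = 0.5) on the primary endpoint (FMA-UE"), with "two-sided α = 0.05, and power (1–β) = 0.80", and states 128 in total, 32 per group. A two-sample t-test with these inputs needs 63.8, so 64 per arm. The figure 128 is therefore 2 × 64, the total for two arms. With 32 per arm the power at d = 0.5 is 50%. That is a separate error. It matters here only as context.

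**Variance of each version of the contrast, in units of 2σ²/n.**
- Raw week-8 difference: 1
- Difference in change: 2(1 − ρ)
- Baseline-adjusted: 1 − ρ²

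The ratios to the adjusted contrast are 1/(1 − ρ²) for raw and 2(1 − ρ)/(1 − ρ²) = 2/(1 + ρ) for change. Both exceed 1 for any ρ strictly between 0 and 1.

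| ρ (assumed) | raw | change | adjusted | excess, raw | excess, change |
|---|---|---|---|---|---|
| 0.3 | 1 | 1.40 | 0.91 | 10% | 54% |
| 0.5 | 1 | 1.00 | 0.75 | 33% | 33% |
| 0.7 | 1 | 0.60 | 0.51 | 96% | 18% |
| 0.8 | 1 | 0.40 | 0.36 | 178% | 11% |
| 0.9 | 1 | 0.20 | 0.19 | 426% | 5% |

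**Check against the model as printed.** Generalized least squares was computed for four arms, five visits and 32 per arm under a random intercept. With free baseline means it returned the raw and change columns. With a common baseline mean across arms it returned the adjusted column. The constraint alone therefore recovers the full gain.

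**Effect on power at 32 per arm.** This depends on which SD stands behind d = 0.5, which the protocol does not say.
- If it is the SD of the score, power at ρ = 0.5, 0.7 and 0.9 is 50% throughout for the raw contrast; 50%, 72% and 99% for change; and 62%, 79% and over 99% for the adjusted contrast.
- If it is the SD of change, the change contrast has 50% power and the adjusted contrast has 62%, 57% and 52%.

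**How far the two readings can differ.** Their difference is the observed baseline imbalance. Under simple randomization its standard error is √(2/32) = 0.25 SD, half the planned effect of 0.5 SD. Stratification by Brunnstrom stage should reduce this by an amount that cannot be derived from the documents.

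**The case against.** A reader might infer that the two sections contradict each other, because change from baseline is zero for everyone at baseline and so cannot be the response in a model with a baseline level. The documents do not support that. The Analysis section does not say that change is the modelled response. The week-8 group-by-time contrast in the printed model is exactly the between-arm difference in change, so both sections can describe one model. That objection stands. What remains is that no sentence makes the link.

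On that reading the larger excesses (96% at ρ = 0.7, 426% at 0.9) belong to the contrast that the Analysis section supports least. The change contrast does use baseline, and its loss is modest when ρ is high. This also stands.

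It can further be said that baseline is not normally entered as a covariate when it is already a level of the response, and that a condensed article may leave parameterization to the analysis plan. The first part is fair, but it explains the omission without recovering the precision. The second part carries less weight, because the article itself prints the time levels, the interaction and the covariate list.

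Finally, randomization is stratified by Brunnstrom stage, which relates to baseline severity. This helps but does not guarantee balance. The four factors give 3 × 2 × 2 × 2 = 24 strata, and 156/24 = 6.5 participants per stratum on average, fewer than one block of 8.

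**Conclusion.** The point holds as a matter of clarity and efficiency. The primary contrast is not tied to a single model term, and either candidate is valid but less precise than a baseline-adjusted contrast. On the better-supported change reading, the excess variance is about 33%, 18% and 5% at ρ = 0.5, 0.7 and 0.9. On the raw reading it is about 33%, 96% and 426%. These figures rest on an assumed ρ, equal variances at baseline and week 8, and complete data. The equal-variance assumption is open to question, since eligibility truncates the baseline score but not the week-8 score. Credit for the listed covariates could shrink the raw figures.

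The calculations show no bias and no inflation of type I error in either contrast taken alone. Nor should a reader infer that baseline adjustment would restore the planned 80% power. It comes close only if d = 0.5 is on the SD of the score and ρ is about 0.7 or higher. If d is on the SD of change, adjusted power over ρ = 0.3 to 0.9 is about 69% down to 52%. The shortfall comes from spreading 128 participants over four arms and needs its own correction.

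**What to change.** State one primary estimand: the difference in mean FMA-UE at week 8, 100 Hz minus 2 Hz, adjusted for baseline FMA-UE. Fit it in one of two ways:
- keep all five visits in the response but constrain the four arms to a common baseline mean, with group effects only at post-baseline visits; or
- use post-baseline visits only as the response, with baseline FMA-UE and baseline-by-time as covariates.

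Then reword the Statistical analysis and Analysis sections so that both name this contrast and this model. If the difference in change is kept instead, say explicitly that the primary test is the week-8 group-by-time contrast and accept the loss shown above.

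The cost is a wording change before unblinding. No visit, measurement or participant is added, because Table 1 already schedules baseline FMA-UE for everyone.
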